#### Reliability assessment

2.3.4

Assessment interviews are audio-recorded and saved to a secure, HIPAA-compliant cloud-based server. Over the course of the study, 10% of interviews will be randomly selected and scored by an independent evaluator. Interrater reliability will be at .80 or higher. If reliability falls below .80, the supervisor will conduct joint interviews with the assessors until a level of .80 or higher is reached in three consecutive interviews.

### Qualitative interviews

2.4

Qualitative interviews were developed by the study team with feedback from the [blinded for review] community advisory board. All qualitative interviews are audio-recorded and transcribed with participant consent using Zoom. Interview recordings and transcriptions are saved to a secure, Health Insurance Portability and Accountability Act (HIPAA) compliant cloud-based server. Participants are compensated following completion of the interview.

#### Study site interviews

2.4.1

Two semi-structured interview guides were developed to capture staff experiences with trauma-informed treatments and perspectives on offering concurrent trauma and substance use treatment. The pre-trial interview guide spans 11 domains including familiarity with PE, perceived benefits and risks of PE among those in SUD treatment, feasibility of incorporating trauma interventions into SUD care, and barriers and facilitators of these interventions within their treatment center. The post-trial interview guide will assess domains relating to implementation of PE including barriers, facilitators, and staff perspectives on the utility of M-PE.

#### Post-treatment participant interviews

2.4.2

Two semi-structured interview guides were developed for the participant interviews with items tailored to the treatment condition. Interviews span several domains including perspectives on treatment offerings, barriers to receiving care, perceived benefits and shortcomings of treatment, and reasons for engaging or withdrawing from treatment.

### Design considerations

2.5

PE is typically delivered in 90-min sessions. We elected to deliver M-PE in 60-min sessions for several reasons 1) recent studies show PE to be as effective with 60 min sessions [52,53], 2) we have found shorter PE sessions to be effective in our own SUD/PTSD treatment research which condenses PE to 60-75 min to make room for SUD intervention [54,55], 3) Berenz et al. used 60-min sessions in their pilot of PE in residential SUD treatment with excellent results [25], and 4) it will be more easily implemented and sustained at [study site] and more easily disseminated to other intensive SUD treatment programs in the future using 60-min sessions. Participants are eligible to participate if they meet full or subthreshold PTSD (i.e., missing no more than one symptom). This decision was based on research demonstrating that those with subthreshold PTSD exhibit similar levels of PTSD severity and impairment to those meeting full criteria [[56], [57], [58], [59]]. Additionally, we considered comparing M-PE to other existing trauma-focused therapies (e.g., Cognitive Processing Therapy). However, comparing M-PE to TAU allows for assessment of how the addition of evidence-based trauma therapy may enhance existing treatment programs.

### Therapist training

2.6

Therapists complete a 2-3-day PE training and are then assigned a training case to complete a full M-PE intervention prior to seeing research participants. For training cases, therapists record all M-PE sessions. Recordings are then listened to, rated for fidelity, and reviewed in twice weekly consultation with a licensed doctoral-level clinical psychologist. The consultant meets regularly with the study MPIs to provide feedback and determine additional training needs prior to assigning therapists to see research participants. Throughout the trial, all M-PE sessions are recorded and twice weekly consultation is ongoing with additional therapist training as needed.

### Fidelity

2.7

Fidelity assessment is two-fold: 1) therapist adherence to the intervention and 2) therapist competency in the delivery of the intervention. Adherence and competency are monitored by clinical consultation with a licensed clinical psychologist, including review of recorded M-PE sessions in addition to evaluation by an independent evaluator. The following standards are used to assess fidelity: 1) treatment manuals with weekly objectives, outcomes, and agendas, 2) therapist training, and 3) ongoing evaluation of treatment fidelity through audio-rating of therapy sessions and supervision. Twice weekly consultation is used to provide corrective feedback as needed and the supervising psychologist completes fidelity rating sheets for each session for the first case post-training. An independent evaluator will rate 10% of sessions at random. Throughout the study course, study therapists keep a session-by-session tracking form with self-ratings regarding use of the manual and covering relevant content. Adverse events (AEs) are monitored at every study contact. Potential AEs are entered into REDCap for review by the two PIs and reported as indicated by institutional and NIH policies.

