## Abstract

Posttraumatic stress disorder (PTSD) and substance use disorders (SUDs) often co-occur and are associated with a more severe clinical profile than either disorder alone. Prolonged Exposure (PE) is empirically supported treatment for PTSD and has demonstrated effectiveness among those with a co-occurring SUD. However, PE is not typically offered in substance use treatment settings, in part due to concerns about feasibility, retention, and symptom exacerbation, as well as structural misfit with time-limited residential and outpatient programs. Massed Prolonged Exposure (M-PE), PE delivered multiple times per week and completed within a condensed timeframe, yields comparable treatment outcomes to PE and may better align with the structure of residential and outpatient care and address key barriers to implementation. Here, we describe an ongoing randomized controlled trial investigating the efficacy of M-PE versus trauma treatment as usual (TAU) delivered concurrent to SUD TAU, among individuals with co-occurring PTSD and substance use disorders enrolled in a comprehensive residential and outpatient SUD program. In addition to examining treatment outcomes, this trial utilizes qualitative methods to gain a deeper understanding of participants’ experiences and evaluate M-PE implementation barriers and facilitators in an SUD treatment setting. We describe the development and implementation of this randomized clinical trial.

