#### Massed prolonged exposure (M-PE)

2.2.2

M-PE follows the structure of PE and includes the following components: 1) breathing retraining, 2) imaginal exposure to the traumatic event, and 3) in-vivo exposures to trauma-related avoided situations. Outside of sessions, participants practice in vivo exposures and listen to session recordings. M-PE is delivered in 60-min sessions 3-4 times per week for 12-16 sessions as indicated by participant needs. Those randomized to M-PE participate in all TAU activities in addition to meeting with their individual M-PE counselor during free periods during typical treatment hours (7:30am to 5:00pm). M-PE is delivered by treatment site providers and research therapists including Master's level therapists and licensed social workers. M-PE providers receive twice weekly supervision by a licensed, Ph.D.-level clinical psychologist and all intervention procedures are overseen by the two study principal investigators.

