#### Self-report measures: in-treatment surveys

2.3.3

In-treatment self-report assessments include the PCL-5, PTCI, BCS, and SUI. This assessment takes approximately 10-15 min to complete. For those randomized to M-PE, in-treatment assessments occur prior to each M-PE session. For participants randomized to TAU, in-treatment assessments are administered twice weekly over 6 weeks to reflect the M-PE survey schedule.

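### Adverse-event capture follows study contact, and contact is more intensive under M-PE, so a by-arm adverse-event count can look higher under M-PE at equal true risk

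*Protocol article*

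**What the plan says.** The rule for adverse events (AEs) is in section 2.7 (Fidelity): "Adverse events (AEs) are monitored at every study contact". What follows capture is also given there: "Potential AEs are entered into REDCap for review by the two PIs and reported as indicated by institutional and NIH policies". The article does not define a study contact and describes no comparison of AE rates between arms.

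The contacts themselves are set out elsewhere.

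- **M-PE (section 2.2.2):** "M-PE is delivered in 60-min sessions 3-4 times per week for 12-16 sessions as indicated by participant needs". These come on top of usual care: "Those randomized to M-PE participate in all TAU activities in addition to meeting with their individual M-PE counselor". Section 2.6 adds that every M-PE session is recorded and that consultation takes place twice a week.
- **Surveys during treatment (section 2.3.3):** "In-treatment self-report assessments include the PCL-5, PTCI, BCS, and SUI". In the M-PE arm they are tied to the sessions: "For those randomized to M-PE, in-treatment assessments occur prior to each M-PE session". In the TAU arm "in-treatment assessments are administered twice weekly over 6 weeks to reflect the M-PE survey schedule".
- **Table 1:** the same four instruments are the only ones marked for the treatment period. The P4 suicide interview has a dash in that column.
- **Section 2.8.1:** self-report goes straight into Qualtrics through a participant link. Whether staff speak with the participant at that time is not stated.
- **Section 2.3:** both arms have the same four blinded interviews after randomization, at the end of treatment (about 6 weeks) and 1, 3 and 6 months later.

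**The concern.** If AEs are noted whenever the study meets the participant, the arm that is met in more depth will tend to yield more recorded events. An M-PE participant sits with a therapist for an hour, three or four times a week. The therapist knows the arm, and the recordings and consultation give a second chance to notice an event. A TAU participant's scheduled study contact over the same weeks is a 10 to 15 minute questionnaire, and its listed content covers PTSD symptoms, cognitions, craving and use. It does not list AEs.

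This matters more here than in most behavioral trials. The Abstract says that PE is not usually offered in substance use programs "in part due to concerns about feasibility, retention, and symptom exacerbation". A by-arm AE table in the final report will be read against that worry. An excess that came only from closer observation would seem to confirm it. A later analysis plan cannot repair this, because events that nobody asked about during TAU treatment are not in the data.

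**Working it through.** The article states no AE rate and no contact total, so there is no figure to reproduce. The check counts the contacts and then shows how far unequal capture could move a by-arm count.

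**Step 1: count the scheduled occasions.**

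- M-PE, in treatment: 12 to 16 sessions (section 2.2.2). The surveys fall just before the sessions, so they add no separate occasion.
- TAU, in treatment: 2 per week × 6 weeks = 12 surveys (section 2.3.3).
- Interviews after randomization: 4 in each arm (section 2.3).

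In treatment the count is 12–16 against 12, a ratio of 1.00 to 1.33. With the interviews it is 16–20 against 16, a ratio of 1.00 to 1.25. The number of occasions is therefore close. The difference lies in what happens at each one.

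**Step 2: a capture model.** Let q be the probability that a session or interview captures a given event, and let f be the yield of a TAU survey relative to a session. Both are assumptions, since the article gives neither. With m sessions and equal true risk:

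- captured in M-PE = 1 − (1 − q)^(m + 4)
- captured in TAU = 1 − (1 − q)^4 × (1 − f·q)^12

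**Step 3: numbers for q = 0.10.**

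- M-PE: 1 − 0.9^16 = 0.815 for 12 sessions, and 1 − 0.9^20 = 0.878 for 16.
- TAU with f = 0: 1 − 0.9^4 = 0.344. Ratios: 0.815/0.344 = 2.37 and 0.878/0.344 = 2.55.
- TAU with f = 0.5: 1 − 0.9^4 × 0.95^12 = 0.645. Ratios: 1.26 and 1.36.
- TAU with f = 1: 1 − 0.9^16 = 0.815. Ratios: 1.00 and 1.08.

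**Step 4: range of the spurious ratio (M-PE/TAU, 12 to 16 sessions).**

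| q | f = 0 | f = 0.25 | f = 0.5 | f = 1 |
|---|---|---|---|---|
| 0.10 | 2.37–2.55 | 1.58–1.70 | 1.26–1.36 | 1.00–1.08 |
| 0.30 | 1.31 | 1.10 | 1.03 | 1.00 |
| 0.50 | 1.07 | 1.01 | 1.00 | 1.00 |

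At q = 0.05 the ratio is 3.02–3.46 for f = 0 and 1.00–1.15 for f = 1, so 2.55 is not a ceiling. The model is crude. It treats every event as open to capture at all contacts and gives an interview the same q as a session. A structured interview that captures more than 10% of events would pull the f = 0 figures down. In no scenario does the ratio fall below 1.

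**The case against.** There is a fair amount to be said on the other side, and most of it limits the point without removing it.

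- **The TAU schedule was built to mirror M-PE.** A reader might infer that TAU participants have no study contact, or only the one interview, before the end of treatment. The article does not support that: section 2.3.3 gives them 12 survey occasions. On the plain wording of the AE rule these may count as contacts, and nothing in the article excludes an AE question at them. The Discussion also mentions reminder calls by study staff. This stands, and it is why the range starts at 1.0.
- **No between-arm AE test is described.** Section 2.7 describes individual safety oversight, and collection at every contact suits that purpose. This also stands. The point concerns any by-arm table that is later drawn from these data.
- **Worsening and relapse do not rest on AE counts.** CAPS-5, TLFB and P4 are given to both arms by blinded assessors at the same interviews, and TLFB covers all days of the study. PCL-5, craving and use are collected in both arms during treatment. The main evidence on exacerbation and relapse is therefore not exposed to this bias.
- **An article leaves AE forms to the full protocol.** True of the forms. But the rule, the session count, the survey contents and Table 1 are stated, and together they set unequal depth of contact.

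Two further readings go too far. One is that AE rates will look higher under M-PE; equal questioning at the surveys would make the ratio close to 1. The other is that control participants are watched less safely. Section 2.2.1 has residential patients in care through the working day on weekdays and outpatients attending up to three days a week, so this is not shown.

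**Conclusion.** The point holds as a risk to comparability. AE capture is tied to contact, and contact during treatment is deeper in M-PE by design: 12 to 16 recorded hour-long sessions against 12 short surveys with no listed AE item. A by-arm count can then look higher under M-PE when the true risk is the same.

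The direction follows from the design. The size does not, because it depends on q and f, which are assumed. It runs from a ratio of 1.0, if TAU surveys elicit events as well as sessions do, to about 2.5, if they elicit none and each other contact captures 10%. With 30% capture or more per contact it is at most about 1.3. If staff already put the same AE questions to TAU participants at each survey, the problem largely goes away and a sentence saying so would settle it. The primary outcomes are not affected.

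**What to change.** 1. Ask one identical structured AE question set in both arms at the end-of-treatment, 1-, 3- and 6-month interviews. Placing it after the CAPS-5 and TLFB keeps an answer that reveals the arm from reaching those ratings.
2. Add one identical AE item to the in-treatment surveys of both arms.
3. Base any between-arm AE comparison on these common sources. The survey windows still differ somewhat: M-PE surveys end with the last session, after 12/4 = 3 to 16/3 = 5.3 weeks, while TAU surveys run for 6. The end-of-treatment question should therefore cover the whole period since randomization.
4. Report all AEs by arm with the source of detection, and list those disclosed in M-PE sessions separately.
5. Leave individual safety reporting from every contact as it is.

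The cost is one short form, one survey item, and someone to review positive survey answers, which must be traceable to the participant. The comparative rate will leave out events known only to M-PE therapists and so could understate harm that arises in sessions. Item 4 is needed for that reason: those events stay in full view, outside the ratio.

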### Data analysis

2.8

#### Data management

2.8.1

Self-report data is captured directly into Qualtrics via anonymous participant links. Interview data is entered into Qualtrics by a member of the study team at regular intervals. Data entry and quality assurance are ongoing with validation and double-entry procedures in place to ensure accurate entry. Additionally, all available data are extracted twice per year and uploaded to the National Data Archives (NDA) following the procedures outlined by the NDA.

#### Treatment outcomes analyses

2.8.2

Primary outcomes comprise the CAPS-5 PTSD severity and TLFB percent days of substance use. PTSD-related cognitions and substance use craving will be examined as potential outcome mediators of intervention effects on the primary outcomes, the remaining follow-up measures discussed above comprise secondary outcomes. Generalized linear mixed models (GLMMs) will be used to model treatment outcomes with the form of GLMM chosen to well-model the respective outcome. The models will include fixed effects for follow-up time, treatment condition, and their interaction together with random intercepts for participants. We expect outcomes to vary by gender, age, race/ethnicity, and baseline PTSD severity so the models will include these as additional fixed effects. Missing data will be addressed using multiple imputation by chained regressions within intervention arms. Wald tests will assess whether there is an interaction between treatment condition and time of follow-up using results aggregated over models fit to the imputed datasets; if there is no such interaction, a Wald test will assess whether there is a main effect for treatment condition.

Secondary exploratory analyses will assess gender as a potential moderator of treatment effects as work has suggested women may show greater treatment gains in trauma-focused therapies compared to men and women have higher rates of developing PTSD prior to an SUD compared to men [27,60]. The potential mediating roles of changes in PTSD-related cognitions and substance use craving on treatment outcomes will be investigated and we will investigate whether changes in PTSD symptomology mediate subsequent changes in substance use outcomes. We will implement multiple analyses to investigate these potential mediation pathways. For each follow-up, we will fit generalized linear models (GLM) for the mediators and outcomes to implement the potential outcomes causal mediation analyses described by Imai et al. [61] These analyses will generate estimates of average direct and average causal mediation effects of the intervention on the outcomes. Alternate longitudinal causal mediation analyses, particularly those examining time-lagged effects of changes in PTSD symptomatology on subsequent SUD outcomes, will develop and employ marginal structural models.

Sample size was determined using Monte Carlo simulation considering uniform 30% dropout over time, correlations between outcomes across time of .30, a group standardized effect for PTSD symptoms and days substance use of .58 (Cohen's d) based on our previous research, and a .05 significance level. A sample size of 168 subjects provides >80% power to identify between group effects under these conditions.

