### Assessments

2.3

Participants complete a baseline interview prior to treatment randomization to establish diagnoses and symptom presentation in addition to interviews at the end-of-treatment (approximately 6 weeks post-randomization) and 1-, 3-, and 6-months post-treatment. Brief self-report assessments are administered 2-3 times per week throughout the treatment course. Participants are compensated for interviews but not for treatment sessions. All assessments are administered by experienced, blinded examiners at the Master's or doctoral-level with a minimum inter-rater reliability of .80 on PTSD and SUD clinical interviews. To determine inter-rater reliability over the study course, 10% of interviews will be randomly selected to be independently scored by licensed, Ph.D.-level researchers. Assessments include a combination of diagnostic interviews and self-report measures. The primary outcomes of interest are changes in PTSD symptoms, substance use frequency and problems, depressive symptoms, and quality of life. Additional focal assessments include measures of trauma-related cognitions and substance use craving. See Table 1 for the assessment schedule.

**Table 1 tbl1:** Patient assessment schedule.

Measure	Purpose	Format	Pretreatment	During Treatment	At End of Treatment	1-, 3-, 6 Month Post-treatment
P-4 Suicide Severity Rating Scale	Eligibility, secondary outcome	Interview	X	-	X	X
Structured Clinical Interview for DSM-5	Characterize Sample	Interview	X	-	-	-
Clinician Administered PTSD Scale-5	Eligibility, Primary Outcome	Interview	X	-	X	X
Timeline Follow Back Interview	Primary Outcome	Interview	X	-	X	X
PTSD Checklist –DSM-5	Secondary Outcome, Mediator, Within Treatment Change	Self-Report	X	X	X	X
Short Inventory of Problems Revised (SIP-R)	Primary Outcome	Self-Report	X		X	X
Substance Use Inventory (SUI)	Secondary Outcome, Within Treatment Change	Self-Report	X	X		
Patient Health Questionnaire-9	Secondary Outcome	Self-Report	X	-	X	X
Brief Inventory of Psychosocial Functioning	Secondary Outcome	Self-Report	X	-	X	X
WHO – Disability Assessment Schedule	Secondary Outcome	Self-Report	X	-	X	X
Brief Substance Craving Scale	Secondary Outcome, Within Treatment Change	Self-Report	X	X	X	X
Posttraumatic Cognitions Inventory	Mediator		X	X	X	X
Treatment Services Review	Characterize Sample, Potential Covariate	Interview	-	-	X	X
Demographic Questionnaire	Characterize Sample, Moderator	Self-Report	X	-	-	-

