#### Assessor administered measures: baseline and follow-up interviews

2.3.1

**PTSD Diagnostic Interview**. The clinician-administered PTSD Scale for DSM 5 (CAPS-5) [36] is the primary PTSD symptom measure. At baseline, the CAPS-5 is used to determine presence of PTSD and pre-treatment PTSD severity. Items are rated on both frequency and intensity to derive a severity score for each symptom ranging from 0 (absent) to 4 (extreme). Items scored at a severity of 2 (moderate) or higher are considered “present” and counted toward the total number of symptoms required for each DSM-5 symptom cluster. DSM-5 requires presence of 1 or more re-experiencing symptoms (cluster B), 1 or more avoidance symptoms (cluster C), 2 or more alterations in cognition or mood symptoms (cluster D), and 2 or more arousal symptoms (cluster E). The present study allows individuals to be subthreshold by 1 symptom. The CAPS-5 also assesses dissociation symptoms, social and occupational functioning, and response validity.

**Substance Use Interviews**. The Structured Clinical Interview for DSM-5 (SCID) [37] is used to assess for presence of SUD(s) at baseline. The Timeline-Follow back (TLFB) [38] is used to assess frequency of substance use and percent of substance use days. At baseline, the TLFB assesses the 90 days prior to baseline. Subsequent interviews assess the period between the last assessment and the current interview date to allow for coverage of all days of the study period. During the TLFB, participants note any dates in which they were in a controlled environment (e.g., residential care, detoxification, hospitalization, incarceration).

**Additional Interview Measures**. Suicidal ideation is assessed using the P4 [39]. This interview assesses current suicidal ideation, plans, and intent as well as history of suicidal thoughts and behaviors. The Treatment Services Review (TSR) [40] assesses participation in various interventions (e.g., individual therapy, residential treatment, detoxification, psychopharmacological intervention) as a total count of times each service was received since the last interview.

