#### Self-report measures: baseline and follow-up surveys

2.3.2

**PTSD Measures.** The PTSD Checklist for DSM-5 (PCL-5) [41,42] is a 20-item self-report measure capturing DSM-5 PTSD Criterion B-E. Items are rated on a 1 to 5 scale with higher scores indicating greater PTSD symptom severity. The Posttraumatic Cognitions Inventory (PTCI) [43] is a 39-item self-report measure capturing cognitions related to traumatic event exposure. Items are rated on a 1 to 7 scale with higher values indicating greater negative cognitions.

**Substance Use Measures.** The Brief Craving Scale (BCS) [44] is a 16-item measure assessing current craving intensity and frequency. The Short Inventory of Problems Revised (SIP-R) [45] is a 17-item measure assessing substance use frequency and associated problems. Items are rated on a 1 to 4 scale with higher values indicating more substance-related problems. The Substance Use Inventory (SUI) [46] is a 7-item measure capturing the quantity and frequency of alcohol and substance since last assessment.

**Treatment Satisfaction.** At the end-of-treatment assessment, participants complete the Client Satisfaction Questionnaire (CSQ-8) [47]. This 8-item self-report measure assesses participant satisfaction with services provided. Items are rated on a 1 to 4 scale with greater values indicating greater satisfaction.

**Additional Measures.** Demographic characteristics are captured at baseline. Depressive symptoms are assessed using the 9-item Patient Health Questionnaire (PHQ-9) [48]. This measure captures depressive symptoms on a 0 to 3 scale with higher scores indicating greater depressive symptoms. The Brief Inventory of Psychosocial Functioning (BIPF) [49,50] is used to assess quality of life and functional impairment. This measure contains seven items rated on a 1 to 7 scale with higher values indicating greater psychosocial impairment. The WHO Disability Schedule 2.0 (WHODAS) [51] is used to assess functional impairment. This 12-item measure assesses impairment in cognition, mobility, self-care, getting along, life activities, and daily life participation.

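### Trauma cognitions (PTCI) are tested as a mediator of CAPS-5 severity, which includes a cognition-and-mood cluster, so shared content can inflate the indirect effect

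*Protocol article*

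**What the plan says.** Treatment outcomes analyses (2.8.2) defines the outcomes: "Primary outcomes comprise the CAPS-5 PTSD severity and TLFB percent days of substance use". It then states that "PTSD-related cognitions and substance use craving will be examined as potential outcome mediators of intervention effects on the primary outcomes". At each follow-up, generalized linear models for mediator and outcome feed a potential-outcomes mediation analysis. Further longitudinal models are mentioned, chiefly for PTSD symptoms acting on later substance use.

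The mediator is the PTCI, which "is a 39-item self-report measure capturing cognitions related to traumatic event exposure" (2.3.2). The outcome is the CAPS-5, an interview whose symptom clusters are listed in 2.3.1. For cluster D the requirement reads "2 or more alterations in cognition or mood symptoms (cluster D". The PCL-5, listed in Table 1 both as a secondary outcome and as a mediator, "is a 20-item self-report measure capturing DSM-5 PTSD Criterion B-E", so it contains the same cluster.

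The article neither sets the cluster D items aside in the cognition pathway nor describes an analysis without them.

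**The concern.** A mediation analysis of cognitions on PTSD severity is read as an answer to a mechanism question: does changing trauma-related beliefs bring down the rest of the disorder? If some items of the outcome record those same beliefs, mediator and outcome correlate through content alone. Treatment that shifts beliefs then moves the PTCI and part of the CAPS-5 together, and the model attributes that part to mediation although no re-experiencing, avoidance or arousal symptom has responded to the change in beliefs.

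The condition for this bias is one the trial expects. The Introduction describes PE as addressing trauma-related cognitions, while trauma TAU (2.2.1) is a coping-skills group without exposure. Mediators are a stated aim in the Introduction and a claimed strength in the Discussion, so a positive result is likely to be interpreted as mechanism.

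**Working it through.** **The plan's own figure.** The article gives no number for the mediation analysis. Its sample size statement (168 participants, d = .58, 30% dropout, .05 level, power above 80%) can be reproduced. With 168 × 0.7 / 2 = 58.8 per arm, .58 × √(58.8/2) = 3.14; 3.14 − 1.96 = 1.18, which gives 88% power at a single visit (two-sided). That figure stands and does not bear on this point.

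**Inputs from the article.** 168 participants with 30% dropout leave 117.6, taken as 118. Allocation is equal. The .58 SD effect is stated for PTSD symptoms and days of substance use.

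**Assumptions, not in the article.**
- The same .58 SD applies to the PTCI.
- PTCI reliability is .85.
- Overlapping items carry a fraction w = .10 to .35 of the total score.
- Those items load λ = .4 to .8 on cognition.
- Every cluster improves by .58 SD, and the non-overlapping items do not depend on cognition given arm.

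**Expected spurious share.** Let δ be the treatment effect on latent cognition.
- Treatment to PTCI: −δ√.85.
- PTCI to total score, given arm: wλ√.85 (the PTCI has unit variance within arm).
- Indirect effect: −.85·δ·w·λ. Total effect: −.58.
- Share = .85·w·λ·δ/.58, which is .85·w·λ when δ = .58.

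Lowest: .85 × .10 × .4 = 3.4%. Highest: .85 × .35 × .8 = 23.8%. Simulation gives about 4-23%. The formula is zero when w = 0 and also when δ = 0.

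**How often the 95% interval excludes zero (simulation, 118 completers).**

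| Setting | Rate |
|---|---|
| δ = .58, overlap 10-35% | about 5-79% |
| of which overlap 10-15% | about 5-20% |
| δ = .3, overlap 30-35% | about 10-31% |
| δ = .3, overlap 10-15% | about 2-8% |
| δ = .58, overlapping items removed | about 3-5% |
| δ = 0, any overlap tried | at most about 6% |

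**Second model, item by item.** This uses 118 completers and 1,500 runs per cell. The 20 symptom items are stated for the PCL-5 and assumed for the CAPS-5. Loadings are .5-.9, and mediation is declared when both paths have p < .05.

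| Overlapping items | δ = 0 | δ = .3 | δ = .58 | δ = .8 | Share at .58 |
|---|---|---|---|---|---|
| 0 | 0.4% | 1.8% | 3.6% | 4.5% | under 1% |
| 2 | 0.7-1.8% | 4-9% | 11-28% | 15-34% | 7-12% |
| 3 | 1.3-3.3% | 8-20% | 20-52% | 24-63% | 10-17% |
| 7 | 4.2-5.0% | 26-33% | 68-81% | 80-98% | 20-34% |

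The row with 7 items counts all of cluster D as cognition, with 7 itself an assumed count. Shares are larger here partly because each non-overlapping item carries a smaller arm effect (√.35 × .58 = .34 SD).

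Both models agree: overlap inflates the mediator-to-outcome path, but an indirect effect appears only if treatment also moves the PTCI.

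**The case against.** A reader might infer that a positive mediation result is nearly guaranteed, that the mediator predicts itself, or that the mechanism aim cannot be answered for cognitions. The documents support none of these.

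- **Nearly guaranteed.** Overlap cannot create a treatment effect on cognitions, and without one the false-finding rate stays at or below about 6%. Even if all 168 are analysed and cluster D is taken as 30-35% of the score and cognition-driven, the rate is 39-93%. Rates close to certainty need all of cluster D counted as cognition and a large effect on the PTCI, but 2.3.1 says cognition or mood.
- **Predicts itself.** The PTCI is a separate self-report scale. The CAPS-5 is an interview, and section 2.3 says "All assessments are administered by experienced, blinded examiners at the Master's or doctoral-level". That reduces shared method, though not shared content.
- **Cannot be answered.** Cognitions are also tested against percent days of substance use, where this overlap does not arise. The PTCI is collected during treatment, so the mediator can be placed before the outcome. Ordering in time does not remove shared content, however.

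Two further objections carry weight. First, if cognitive change truly improves cluster D symptoms, the indirect effect on total severity is real as defined. What is in doubt is its reading as an effect on other symptoms. Second, leaving out all of cluster D also removes mood symptoms and could hide a genuine effect on them. Both argue against replacing the planned outcome, but not against showing a second one.

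Finally, the paragraph containing the mediation plan opens as secondary and exploratory, and a full analysis plan, not shown, might already contain such an analysis. That lowers the weight of the point. The pairing itself is nevertheless stated in the article.

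**Conclusion.** The concern holds in a limited form. The plan pairs a cognition scale with a severity score that includes a cognition-and-mood cluster, and the shared content can inflate the indirect effect on CAPS-5 severity when M-PE changes cognitions more than TAU does. The wide range of the results reflects how little the documents fix: the amount of overlap, the loadings, the PTCI's reliability and the treatment effect on it are all assumed. The direction of the bias does not depend on those values, provided the overlapping items track cognition in the same direction as the PTCI.

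The point is confined to the exploratory cognition-to-PTSD pathway. It leaves the primary treatment comparison and the cognition-to-substance-use pathway untouched.

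**What to change.** For the PTCI mediation analyses only:

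1. Keep CAPS-5 total severity as the planned outcome.
2. Prespecify a companion analysis with the CAPS-5 score without cluster D (clusters B, C and E), reported beside the total. Do the same for the PCL-5 wherever it is paired with the PTCI.
3. State in advance that cognitive mediation of PTSD symptoms beyond content overlap will be claimed only if it also holds for the score without cluster D.

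The cost is one derived score from items already collected and a sentence or two in the analysis plan. The trial is ongoing, so this can be settled before results are known. The downside is that the part score is less familiar and somewhat less reliable than the total, and it drops mood symptoms along with cognitions. A null companion result should therefore be read as failure to show mediation beyond overlap, not as evidence that cognitions play no part.
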